# 5. adverse events

## 5.1 Definitions

**Adverse Event (AE):** any untoward medical occurrence in a patient or clinical study subject.

**Serious Adverse Event** **(SAE):** any untoward and unexpected medical occurrence or effect that:

- **Results in death**
- **Is life-threatening** – *refers to an event in which the subject was at risk of death at the time of the event; it does not refer to an event which hypothetically might have caused death if it were more severe*
- **Requires hospitalisation, or prolongation of existing inpatients’ hospitalisation**
- **Results in persistent or significant disability or incapacity**
- **Is a congenital anomaly or birth defect**

Medical judgement should be exercised in deciding whether an AE is serious in other situations. Important AEs that are not immediately life-threatening or do not result in death or hospitalisation but may jeopardise the subject or may require intervention to prevent one of the other outcomes listed in the definition above, should also be considered serious.

## 5.2 Reporting Procedures

All adverse events should be reported. Depending on the nature of the event the reporting procedures below should be followed. Any questions concerning adverse event reporting should be directed to the Chief Investigator in the first instance.

**5.2.1 Non serious AEs**

All such events, whether expected or not, should be recorded.

**5.2.2 Serious AEs**

An SAE form should be completed and faxed to the Chief Investigator within 24 hours. However, relapse and death due to stroke (or diabetes in participants with diabetes), and hospitalisations for elective treatment of a pre-existing condition do not need reporting as SAEs.

All SAEs should be reported to the <name of REC> where in the opinion of the Chief Investigator, the event was:

- ‘related’, ie resulted from the administration of any of the research procedures; and
- ‘unexpected’, ie an event that is not listed in the protocol as an expected occurrence

Reports of related and unexpected SAEs should be submitted within 15 days of the Chief Investigator becoming aware of the event, using the NRES SAE form for non-IMP studies. The Chief Investigator must also notify the Sponsor of all SAEs.

Local investigators should report any SAEs as required by their Local Research Ethics Committee, Sponsor and/or Research & Development Office.

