## 6.2 Enrollment and study conduct

Following informed consent/assent the research team will collect full medical and medication history, as well as historic bloods from Cerner (hospital computer system) as per routine clinical care. In addition to the admission blood tests, venous blood (<20 ml) will be taken on admission and at 24 and 72 hours for measurement of biochemical, metabolic and hormonal profiles (including, but not limited to: glucose, HbA1c, c-peptide, CRP and other markers of neuro-inflammation). Blood samples (whole blood and plasma) will be stored temporarily in a -20 degree freezer (frozen within 24 hours) at Charing Cross Hospital and transported in bulk by courier on dry ice to a -80 freezer at St Mary Hospital for the use in future research. If participants meet the inclusion criteria they will be enrolled on to the study immediately.#

We do not anticipate that any significant incidental findings will arise as the data pulled from Cerner will be retrospective and much of the sample analysis is done post-hoc. If participants in the “non-diabetes” cohort return blood results that indicate that they have diabetes we will inform their clinical team so that they can manage this appropriately.

Blinded continuous glucose monitoring (CGM) will be applied to 100 consecutive volunteers with an acute stroke (NIHSS score >6) and a previous diagnosis of diabetes who are admitted to Charing Cross Hospital and 100 people with an acute stroke (NIHSS score >6) without diabetes in a 1:1 ratio. This will be done as soon as is feasible after admission. Clinical team will be instructed to test participants capillary blood glucose as per standard care, and if symptoms of hypo- or hyperglycaemia occur. Sensors will be worn for a maximum of 10 days (whilst in hospital) but will be removed on hospital discharge should this occur before 10 days are up. Glucose alerts will not be enabled as the CGM will be blinded.

CGM involves insertion of a small plastic cannula to the subcutaneous tissue of the abdominal skin by members of the study team. The cannula is attached to a small data logger which will be taped to the patients’ skin. CGM will take place for 10 days, throughout the participants stay in hospital.

If the participants’ sensor fails or falls out the research team will provide a new sensor and will help the participant to insert it. .

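### The SAE definition shuts out expected serious events, and a fatal glucose event attributed to diabetes in a participant with diabetes need not reach the 24-hour report or the sponsor

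*Protocol*

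**What the plan says.** Four parts of protocol section 5 bear on this point.

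- **5.1 Definitions.** An adverse event is any untoward occurrence, with no condition on expectedness. An SAE is "any untoward and unexpected medical occurrence or effect that" meets one of the listed seriousness criteria, such as death.
- **5.2 Reporting Procedures.** It opens by asking for every adverse event to be reported, then sends the reader to the procedures beneath it according to the nature of the event.
- **5.2.1 Non serious AEs.** Expectedness makes no difference here: "All such events, whether expected or not, should be recorded". No deadline is attached.
- **5.2.2 Serious AEs.** This route does have a deadline: "An SAE form should be completed and faxed to the Chief Investigator within 24 hours". Some events are then taken out: "relapse and death due to stroke (or diabetes in participants with diabetes"), together with elective admissions for existing conditions, "do not need reporting as SAEs". The ethics committee receives SAEs that the Chief Investigator judges both related and unexpected, the latter meaning "ie an event that is not listed in the protocol as an expected occurrence". Finally, "The Chief Investigator must also notify the Sponsor of all SAEs".

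Section 6.2 (Enrollment and study conduct) sets the context: "Glucose alerts will not be enabled as the CGM will be blinded". Ward staff continue capillary glucose testing as in usual care, and also when symptoms suggest low or high glucose.

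**The concern.** There are two separate faults.

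The first is where expectedness sits. Whether an event is serious is one question, and whether it was foreseen is another. Section 5.1 merges them and section 5.2.2 treats them as distinct. As written, a serious event that someone regards as expected has a less definite route than a trivial expected one.

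The second is the reach of the exemption for diabetes deaths. It operates before anyone is required to consider a link with the study, and it contains no exception for deaths in which glucose played a part. The study is about glucose, inserts a sensor, and keeps the sensor readings from the clinical team. A glucose-related death is one that the Chief Investigator and sponsor would want to examine promptly, if only to conclude that the study had nothing to do with it. The rule also differs between the two groups the study recruits.

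**Working it through.** No figure in the protocol underlies this point, so the check is to trace events through the rules.

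**Step 1: the definition against the reporting section.** If every SAE is unexpected by definition (5.1), the expectedness test for the ethics committee in 5.2.2 can exclude nothing. The test does work only if some SAEs are expected, so 5.2.2 is written as though 5.1 did not contain the word.

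**Step 2: a serious event judged expected.**

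- Section 5.2.1 covers expected events, but only non-serious ones, so it does not apply.
- Section 5.2.2 covers SAEs, and under 5.1 this event is not one, so it does not apply either.
- Section 5.2 applies, because the event is still an adverse event. That general statement gives neither a time limit nor a recipient, and it points to the two subsections that have just failed to cover the event.

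**Step 3: a fatal glucose event.**

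| Participant and attribution | Diabetes exemption | 24-hour form and sponsor notice |
|---|---|---|
| With diabetes, death attributed to diabetes | Applies | Neither is required |
| With diabetes, death attributed to another non-exempt cause, for example treatment | Does not apply | Required if judged unexpected |
| Without diabetes, not attributed to stroke | Does not apply | Required if judged unexpected |

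The protocol does not say whether a hypoglycaemic or hyperglycaemic death counts as due to diabetes. The choice between the first two rows is left to the person reporting.

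**Step 4: the sponsor.** The sponsor sentence covers all SAEs and has no exemption of its own. One could argue that an exempt death is still an SAE and so still notifiable. But the Chief Investigator has to learn of it first, and the 24-hour form is the stated channel for that. For exempt deaths the form is not required. On the natural reading, neither the Chief Investigator's judgement of relatedness nor the sponsor notice is assured.

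**Step 5: how many participants the clause can reach.** The plan is 200 participants in a 1:1 ratio, so 200 / 2 = 100 have diabetes. This is the number to whom the clause could apply, not a number of events.

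**The case against.** The case on the other side has several good points.

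- **The exemption is permissive and narrow.** It says that reporting is not needed, not that it is forbidden. It covers only participants with diabetes and only deaths attributed to diabetes. A death put down to the sensor, or to treatment, is not exempt. All of this stands, which is why the conclusion is that such a death *need not* reach the report. A reader might infer that it *would not*; the text does not support that.
- **Expected serious events are not without any duty.** Section 5.2 still asks for all adverse events to be reported. This stands too. What is lacking is a deadline and a recipient.
- **The repeated word may have little effect in practice.** Section 5.2.2 treats an event as unexpected unless the protocol lists it as expected. I found no such list in the text available, apart from the exemptions themselves. If that test also governs 5.1, most serious events remain SAEs. This limits the practical effect of the first fault, but 5.1 does not refer to that test, and the two sections still conflict.
- **Usual glucose testing continues, and outcomes are collected.** Capillary testing goes on, severe hypoglycaemia and 90-day mortality are secondary outcomes, and section 4.4 makes a serious study-related event a ground for withdrawal. These lower the chance that a glucose event is missed, and they rule out any claim that such deaths would go unseen. None of them supplies a 24-hour or sponsor route.
- **Exempting events of the underlying disease is a deliberate choice.** That is reasonable, and it is the reason to narrow the diabetes clause rather than remove it.

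A reader might also put a number on the fault by applying the approximate 10% early mortality in section 6.1 to the sample: 200 × 0.10 = 20 deaths. The documents do not support that use. The rate describes acute stroke in general, section 6.1 leaves out patients who have died or are on an end-of-life pathway when identified, and the rate covers all causes. It says nothing about deaths attributed to diabetes.

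**Conclusion.** The point holds in a limited form. Sections 5.1 and 5.2.2 conflict on whether expectedness is part of being an SAE, and on a literal reading a serious expected event is left with a duty that has no deadline or recipient. Separately, a fatal glucose event attributed to diabetes in a participant with diabetes need not be reported within 24 hours or notified to the sponsor. The same event in a participant without diabetes is outside that exemption.

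The size cannot be given as a number of deaths. The diabetes clause can apply to half of the planned sample, and its effect depends on how the reporter attributes the death. The conclusion assumes that exempt deaths are outside the sponsor notice as well as the form, which is the natural reading but not the only possible one. It does not imply that blinded monitoring causes harm; the documents give no evidence of that. This is a fault in stated safety rules that should be corrected by amendment.

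**What to change.** Reconcile sections 5.1 to 5.2.2 with two changes.

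1. In 5.1, delete the words *and unexpected* from the SAE definition. Every event meeting a seriousness criterion then falls under 5.2.2, and expectedness is tested once, at the ethics-committee step.
2. In 5.2.2, narrow the diabetes exemption so that it does not cover deaths in which low or high glucose played a part, or in which a link with a study procedure is possible. Such deaths should go through the 24-hour form and the sponsor notice in both cohorts, so that the Chief Investigator judges relatedness with the report in hand.

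The stroke exemption can stay. The cost is a short amendment and a few more SAE forms; data collection and analysis do not change.

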## 6.1 Recruitment and consent

Recruitment will be undertaken in collaboration with the Stroke team of Charing Cross Hospital in London. Participants will be identified via the emergency departments following an acute stroke and participant information sheets will be given to potential subjects. If a participant is unable to provide verbal consent, assent will be sought from their carer, In line with the Mental Capacity Act 2005 (MCA) which covers research involving adults (aged 16 years and over) who lack capacity in England and Wales.

Where possible, Informed consent will be obtained. Hospital research staff will approach the patient to discuss the study and provide a patient information sheet. After allowing sufficient time for a decision about whether to take part in the study and an opportunity to ask questions, consent will be obtained in writing.

When a patient has mental capacity but is unable to sign the consent form (e.g. because of weakness of the dominant hand following stroke), consent is confirmed orally in the presence of a witness (an individual not otherwise involved in the trial), and the witness signs and dates the consent form on behalf of the participant.

It is anticipated that approximately one third of study-eligible patients will be unable to engage with an informed consent process due to the effects of stroke upon communication and cognition. As exclusion of this group would drastically reduce the clinical relevance of the study, if a patient has been identified as eligible but lacks the capacity to consent, a personal or nominated consultee is approached.

Hospital research staff first attempt to identify an appropriate personal consultee (usually the next of kin) in order to discuss the study and provide a consultee information sheet. If a personal consultee is identified, after allowing sufficient time for him/her to consider the patient’s wishes and feelings and an opportunity to ask questions, the consultee is asked to complete a consultee declaration form if he/she believes the patient would have no objection to taking part in the study.

If an appropriate personal consultee cannot be located, an independent clinician (nominated consultee) is asked to confirm that the patient lacks capacity for con- sent, and that study participation would not introduce a risk of harm or be against the patient’s wishes from what is known about the patient’s character and beliefs. The independent clinician signs an independent clinician declaration form concerning study participation.

If the communication or cognitive difficulties that impeded a patient’s ability to provide consent are still present at 90 days after stroke, where a personal consultee provided permission to enter the study, this person will be contacted to complete the 90 day study-specific outcome questions on behalf of the patient. In cases where an independent clinician provided permission for study participation, the participant will be contacted and if unable to respond, a personal consultee will be contacted.

The early mortality rate following acute stroke is approximately 10%. These patients are usually identified soon after admission and treated palliatively. However, unexpected deaths also occur.

When a patient has died, or if a formal palliative end of life care process has been started at the point when the patient is identified as eligible for the study, individual patient consent will not be possible, and it is likely to be distressing for a personal consultee to be approached regarding the research use of routinely collected health- care data. Acute stroke has many effects upon neurological function and consciousness which can fluctuate for several days or even weeks.

However, these are likely to be challenging clinical situations where seeking an alternative method of consent will be difficult because of the severe degree of remaining neurological impairment and the time elapsed since admission. In these unusual scenarios, an alternative method of consent will not be pursued, and the patient will not be included.

## 6.2 Enrollment and study conduct

Following informed consent/assent the research team will collect full medical and medication history, as well as historic bloods from Cerner (hospital computer system) as per routine clinical care. In addition to the admission blood tests, venous blood (<20 ml) will be taken on admission and at 24 and 72 hours for measurement of biochemical, metabolic and hormonal profiles (including, but not limited to: glucose, HbA1c, c-peptide, CRP and other markers of neuro-inflammation). Blood samples (whole blood and plasma) will be stored temporarily in a -20 degree freezer (frozen within 24 hours) at Charing Cross Hospital and transported in bulk by courier on dry ice to a -80 freezer at St Mary Hospital for the use in future research. If participants meet the inclusion criteria they will be enrolled on to the study immediately.#

We do not anticipate that any significant incidental findings will arise as the data pulled from Cerner will be retrospective and much of the sample analysis is done post-hoc. If participants in the “non-diabetes” cohort return blood results that indicate that they have diabetes we will inform their clinical team so that they can manage this appropriately.

Blinded continuous glucose monitoring (CGM) will be applied to 100 consecutive volunteers with an acute stroke (NIHSS score >6) and a previous diagnosis of diabetes who are admitted to Charing Cross Hospital and 100 people with an acute stroke (NIHSS score >6) without diabetes in a 1:1 ratio. This will be done as soon as is feasible after admission. Clinical team will be instructed to test participants capillary blood glucose as per standard care, and if symptoms of hypo- or hyperglycaemia occur. Sensors will be worn for a maximum of 10 days (whilst in hospital) but will be removed on hospital discharge should this occur before 10 days are up. Glucose alerts will not be enabled as the CGM will be blinded.

CGM involves insertion of a small plastic cannula to the subcutaneous tissue of the abdominal skin by members of the study team. The cannula is attached to a small data logger which will be taped to the patients’ skin. CGM will take place for 10 days, throughout the participants stay in hospital.

If the participants’ sensor fails or falls out the research team will provide a new sensor and will help the participant to insert it. .

Recent data has demonstrated that the Dexcom G6 sensor and data logger are able to go through an MRI machine so if the participant requires an MRI scan as part of their clinical care (independent to the study) they can wear the sensor and data logger throughout.

## 6.3 Telephone follow up at 3 months

Participants who are discharged from the hospital within 3 months will be followed up by the research team via a telephone call (in order to obtain MRS scores).

Participants will be given the option to provide consent to be contacted again for future research.

End of study will be defined as Last Subject Last Visit (LSLV)

7. STATISTICs and data analysis

This is a hypothesis generating study and, as such, we are not proposing a fully-powered study. The data gathered from the proposed work will serve as robust pilot data to support a larger randomised study. At the end of the study, participants with impaired glucose tolerance or diabetes will be sub analysed.

Parametric data will be compared using an independent t-test. Non-parametric data between groups will be compared using a Mann-Whitney test.

Data and all appropriate documentation will be stored for a minimum of 10 years after the completion of the study, including the follow-up period.

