## 1.2 Rationale for current study

Increased glycaemic variability is associated with worse outcome in patients with diabetes after acute stroke.

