**Stroke Primary outcomes:**

Modified Rankin Scale (MRS) at 90 days

National Institutes of Health Stroke Scale (NIHSS) at 24, 48 and 72 hours

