## 8.3 Confidentiality

The Chief Investigator will preserve the confidentiality of participants taking part in the study and is registered under the Data Protection Act. Confidentiality of data will be preserved during data transmission via the use of anonymised codes. Participants will be assigned codes based on order of enrolment and site at which they are enrolled (G-VAS-001 etc.). Identifiable personal information will be stored securely in a locked room at Imperial College Healthcare NHS Trust and Imperial College London. Pseudonymised data will be stored on Imperial College Healthcare NHS Trust computers, Imperial college London computers or encrypted laptop computers (either ICL/ICHT). Data will be accessible only to the Research Team and for audit. Pseudonymised data will be used for analysis. The data will be stored at Imperial College London for 10 years. The data custodian is [name].

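### The 90-day MRS, a primary outcome, is taken by telephone by the research team, which knows diabetes status and has access to study data, and the visible text does not blind the rater

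*Protocol*

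**What the plan says.** The protocol lists "Modified Rankin Scale (MRS) at 90 days" among the stroke primary outcomes in Section 2. Section 6.3 says how it is obtained for participants who have left hospital within 3 months: they "will be followed up by the research team via a telephone call (in order to obtain MRS scores").

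Four other places show what that team knows or can reach:

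- **History (Section 6.2).** At entry "the research team will collect full medical and medication history", and recruitment is by diabetes status, 100 with and 100 without.
- **Sensors (Section 6.2).** "If the participants’ sensor fails or falls out the research team will provide a new sensor". The cannula is inserted by members of the study team.
- **Data access (Section 8.3).** "Data will be accessible only to the Research Team and for audit".
- **Expectation (Section 1.2).** "Increased glycaemic variability is associated with worse outcome in patients with diabetes after acute stroke".

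The only blinding described is in Section 6.2: "Glucose alerts will not be enabled as the CGM will be blinded". The sensor is worn for at most 10 days. Section 6.1 adds that, where communication or cognitive difficulties persist at 90 days, a consultee may answer the outcome questions.

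**The concern.** Placing a patient on the MRS takes judgement, especially between adjacent grades and over the telephone. That is general methodological knowledge; the protocol does not say it. If the rater knows the exposure, or a close marker of it, and expects a direction, borderline grades can drift that way. The drift would then look like an effect of glycaemic variability or of diabetes.

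The word blinded in Section 6.2 could lead a reader to think this is covered. It is not: it hides readings while the sensor is worn and says nothing about the person who calls at 90 days.

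The study is declared hypothesis generating, but Section 7 intends its data to support a larger randomised study, so a spurious association would be carried forward. Who rates, and what the rater knows, is study conduct and belongs in the protocol rather than in an analysis plan.

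**Working it through.** The protocol gives no alpha, power, effect size or expected MRS distribution, so there is no figure of its own to reproduce. The check has two parts.

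**1. The text, side by side**

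| Question | What the visible text gives |
|---|---|
| Who obtains the 90-day MRS? | The research team, by telephone, for those discharged within 3 months (6.3) |
| Who scores those still in hospital at 90 days? | Not stated |
| Does the team know diabetes status? | Yes: it takes the history (6.2) |
| Can the team reach sensor data? | It has access to study data (8.3), with no restriction on timing |
| When does blinding of the device stop mattering? | When wear ends, by day 10 at the latest; 90 − 10 = 80 days before the MRS is due |
| Is the rater blind to sensor results or cohort? | Not stated in 6.2, 6.3 or 8.3; Appendices 1 and 2 are figures that cannot be seen |

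**2. What differential grading could do (illustration only)**

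*Inputs.* The groups of 100 and 100 match the 1:1 cohort sizes in Section 3. Everything else is assumed: no true difference, two-sided 0.05, the poor-outcome rates, the MRS distribution and the share mis-scored.

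*(a) MRS cut into good and poor.* A share m of truly good outcomes is scored poor in one group, so p2 = p1 + (1 − p1)m. The chance of a significant difference in the direction of the shift is Φ[(p2 − p1 − 1.96·SE0)/SE1], where SE0 = √[2p̄(1 − p̄)/100], p̄ is the mean of p1 and p2, and SE1 = √[(p1(1 − p1) + p2(1 − p2))/100].

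For p1 = 0.50 and m = 0.10: p2 = 0.55, SE0 = 0.0706, SE1 = 0.0705, so Φ[(0.05 − 0.1384)/0.0705] = Φ(−1.25) = 0.105.

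| True poor-outcome rate | 10% of good mis-scored | 20% of good mis-scored |
|---|---|---|
| 30% | 18.0% | 53.6% |
| 40% | 13.5% | 39.8% |
| 50% | 10.5% | 29.4% |
| 60% | 8.4% | 21.6% |

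*(b) Full ordinal scale.* Section 7 names the Mann-Whitney test. It was simulated 4,000 times with 100 per group and assumed proportions 0.08, 0.14, 0.14, 0.14, 0.20, 0.12 and 0.18 for grades 0 to 6. With no mis-scoring the test rejected in 4.65% of runs.

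| Chance that an eligible patient moves one grade | Upward in one group only | Opposite shifts in both groups |
|---|---|---|
| 10% | 5.6% | 7.5% |
| 20% | 8.9% | 17.6% |
| 30% | 11.8% | 34.0% |
| 40% | 18.3% | not run |

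Upward moves applied to grades 0 to 4, downward moves to grades 1 to 5. Deaths (grade 6) were never moved.

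*(c) On the odds-ratio scale.* Assume two halves of 100, 50% truly poor in each, and d patients moved to poor in one half and d to good in the other. Then OR = [(50 + d)/(50 − d)]², with standard error of log OR √{2[1/(50 + d) + 1/(50 − d)]}.

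| d | OR | 95% Wald interval |
|---|---|---|
| 3 | (53/47)² = 1.27 | 0.73 to 2.22 |
| 5 | (55/45)² = 1.49 | 0.86 to 2.61 |
| 8 | (58/42)² = 1.91 | 1.09 to 3.34 |

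Differential grading can create an association where none exists. Small one-grade drift in one group does little on the ordinal scale; shifts in opposite directions do more.

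**The case against.** **The caller may never see a trace.** A reader might infer that the person who telephones has seen the glucose data. The documents do not support that. Section 6.3 names a team, not a person, and Section 8.3 gives access at team level. No section says that sensor files are opened or MAG computed before day 90. Appendix 2, on data flow, might settle the matter but is not visible. This stands: bias through glucose values is possible, not shown. Knowledge of diabetes status is better documented, since the team takes the history and recruits by cohort.

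**The odds ratios are not estimates.** The protocol specifies neither a split at median MAG nor a cut at MRS 2/3. A rater could not know a cohort median before the cohort is complete. Two of the three intervals in (c) include 1. This stands.

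**The scope is partial.** The call covers only those discharged within 3 months, and deaths cannot be mis-graded, so fewer than 200 scores are exposed to this. Section 6.1 mentions outcome questions specific to the study, so some question set is foreseen, though not described.

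**The expectation is not uniform.** Section 1.2 refers to patients with diabetes. Section 1.1 cites one study in which the association was lost at 3 months and one, in people without diabetes, in which it was present.

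**Other outcomes give a check.** NIHSS at 24, 48 and 72 hours falls within planned blinded wear, and 90-day mortality is immune to grading. Grading driven only by cohort would also largely drop out of an analysis of MAG within each cohort. It is therefore too strong to say that analysis can do nothing. None of this corrects MRS scores influenced by the trace, or a comparison of MRS between the cohorts.

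**Conclusion.** The point holds in a limited form. As written, a judgement-based primary outcome may be rated by someone who knows the cohort and possibly the glucose results, and the visible text contains no safeguard. Blinding of the sensor during wear does not supply one.

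The amount of bias cannot be derived from the documents. Under the assumptions above, a false-positive chance of nominally 5% becomes about 6% to 18% when 10% to 40% of eligible patients drift one grade in one group, and about 8% to 34% when 10% to 30% drift in opposite directions. These figures show what is possible. They are also upper-side illustrations, because they treat every survivor as scored by an unblinded caller.

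The study is observational and hypothesis generating, which lowers the consequence. This is a cheap improvement worth making, not a flaw that invalidates the study.

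**What to change.** State in Section 6.3 that:

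1. For each participant, no sensor trace is viewed and no MAG or other glucose metric is computed until that participant's 90-day MRS is entered and locked. The one exception is confirming, at sensor removal, that a data file exists.
2. The MRS is scored with a fixed structured question set, including when a consultee answers and for those still in hospital at 90 days.
3. Where possible, the call is made by an existing team member who did not enrol the participant and is not told the cohort.

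Diabetes may still come up in conversation, and step 1 does nothing about it, so remaining knowledge of diabetes status should be reported as a limitation. If the appendix figures already contain such a barrier, Section 6.3 should refer to it.

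The cost is protocol wording and a change in the order of data processing; sample size is unchanged and no extra staff are needed. The downside is that sensor quality checks and summaries come about 80 days later than they otherwise could.
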